## Abstract

**Background:**

Schools present venues for physical activity promotion among youth, with physical education (PE) considered the primary vehicle responsible for increasing activity levels. Yet students are not very physically active during typical school PE classes. With the aim to engage Hong Kong students in more moderate-to-vigorous physical activity (MVPA) during PE, a fitness infusion intervention using rope skipping was designed, and its effectiveness will be examined. Rope skipping was chosen because a) it provides moderate-to-high intensity physical activity; b) is inexpensive; c) students find it enjoyable; and d) is feasible in typical environments in Hong Kong, where PE classes are large in size (up to 40 students) and space available for physical activity is usually limited.

**Methods/Design:**

A matched-pair cluster randomized controlled trial was designed. Secondary school students from 24 classes (from 12 schools) will be recruited to participate in the trial. Students’ baseline MVPA will be measured during school PE. Classes will be matched according to baseline variables and one class from each pair will be randomized into the experimental group. Teachers in the experimental group will be invited to attend a teacher workshop, and will insert a 15-minute rope skipping activity in four consecutive PE lessons. Motivational factors based on self-determination theory will also be measured as secondary outcomes. The effectiveness of the intervention will be evaluated by comparing changes in the proportion of lesson time spent in MVPA from baseline to follow-up across the experimental and control groups.

**Discussion:**

Physical activity levels in PE are often very low and there is a need to identify feasible low-cost interventions that can be easily disseminated. If the results of the study suggest the intervention to be effective, it could be implemented to schools throughout Hong Kong and other cities where space is limited.

**Trail registration:**

ANZCTR: ACTRN12613000968774. Registered on 30 August 2013.

## Background

Despite the extensive physical and psychological health benefits of physical activity (PA) [1,2], many children and adolescents are not sufficiently active [3,4]. One way of promoting PA in this population is through school physical education (PE), which provides a venue for all students to engage in moderate-to-vigorous physical activity (MVPA) and accrue immediate health benefits [5]. Apart from that, another important role of PE is to provide students with knowledge, skills, and confidence to stay active throughout their lifetime [5]. Through PE, students can also acquire self-management skills, and to experience and learn about different types of games and activities [6]. Nonetheless, to counter low habitual PA levels, it has been suggested that school PE should be designed to keep students active for at least 50% of the class time [7]. Unfortunately, activity levels in PE are often very low, with students spending only 27% to 47% of their lesson time in MVPA [8]. Furthermore, results of studies conducted in Hong Kong suggested that most students are insufficiently active during PE periods (Ha et al.: Autonomous motivation predicts moderate-to-vigorous physical activity and psychological well-being in Hong Kong schoolchildren, submitted).

Considering the low levels of PA in many PE lessons and the potential health benefits of PA, interventions are needed to increase students’ accumulation of MVPA during PE. In a recent review and meta-analysis of interventions designed to increase MVPA in PE, Lonsdale and colleagues [6] found that fitness infusion interventions (i.e., the integration of vigorous physical activity into other activities) were effective in increasing students’ PA levels during PE. However, the authors noted the lack of high quality studies evaluating fitness infusion interventions and the need for further work in this area. Therefore, the aim of our study was to design and evaluate the effectiveness of an intervention intended to increase students’ MVPA during PE in Hong Kong.

Researchers have found that there is a decline in PA levels with age in children and adolescents [9], therefore our intervention was specifically aimed at secondary school adolescents. Rope skipping was chosen as an activity to be used as part of our intervention. This activity was chosen for numerous reasons. First, rope skipping is a form of moderate-to-high intensity PA [10], thus can be considered as an appropriate fitness infusion tool. Second, rope skipping is low-cost, and therefore could be promoted to schools and students from lower socioeconomic classes. This is important because studies have found that adolescents of lower, compared with higher, socioeconomic statuses may be less physically active [11]. Therefore, the designed intervention could be applicable to all schools and students. Thirdly, students, particularly girls, found rope skipping to be an enjoyable activity [12]. Finally, Hong Kong is one of the most densely populated cities in the world, and schools typically have little space for students to engage in PA [4]. Rope skipping is an activity which does not require a lot of space, hence is suitable for the specific school environments in Hong Kong [13].

### Motivational determinants of physical activity participation

Although the primary aim of PA promotion interventions are to increase students’ instantaneous MVPA, the long-term effects of the intervention in terms of supporting future PA participation should also be considered. As motivational factors are strong precursors to future behaviors, indicators of these constructs should also be used to evaluate an intervention. Specifically, interventions could be considered as more successful if they facilitate types of motivation that support long-term persistence in PA. According to self-determination theory (SDT) [14], motivation can be broadly classified into autonomous (i.e., engaging in an activity for fun and enjoyment or to attain valued outcomes) and controlled (i.e., avoiding self-guilt or acting under pressure from others) forms of motivation. Researchers have shown that autonomous motivation positively predicted students’ percentage of time spent in MVPA during PE [15,16]. In contrast, time spent in MVPA was either negatively associated with [16], or was unrelated to [15], controlled forms of motivation. As autonomous motivation is related to persistence in an activity and psychological well-being [14], while controlled motivation may be detrimental to long-term engagement, the intervention should be evaluated based on students’ changes in these types of motivation towards PE. A “successful” intervention should not only increase students’ PA levels, but also promote more autonomous forms of motivation. Further, it should not increase students’ controlled motivation. Within SDT, the quality of teacher-student interaction may also support or undermine students’ PA engagement. Specifically, the degree to which teachers are autonomy supportive may affect students’ motivation in PE [17]. Autonomy supportive behaviors include promoting fun and enjoyment in students, or providing meaningful rationales for activities. Perceived autonomy support of teachers was found to be associated with students’ autonomous motivation toward PE [18,19]. In this study, we propose to examine whether perceived autonomy support may be associated with students’ autonomous motivation to PE, and therefore their engagement in PE.

### Objectives of current study

The main objective of the current trial is to examine whether the implementation of a 15-minute rope skipping activity at the start of PE lessons would increase secondary school students’ percentage of time spent in MVPA during their classes. Changes in autonomous and controlled forms of motivation towards PE, as secondary outcomes, will also be used to evaluate the effectiveness of the intervention. The intervention will be implemented by the PE teachers, assisted by rope skipping ambassadors provided to schools [12]. The main roles of ambassadors will be to assist teachers in running the classes, demonstrate rope skipping skills taught by the teacher, and to ensure teachers adhere to the structured plan provided to them during the training. As the intervention will be delivered at the class level, a cluster (i.e., class) randomized controlled trial was considered to be the most appropriate study design. Specifically, the intervention will be implemented in classes assigned to the experimental group for four consecutive lessons. While teachers of classes allocated in the control (i.e., delayed intervention) group will employ usual teaching practices during the experimental period. We hypothesize that students’ autonomous motivation towards PE would predict higher percentages of time spent in MVPA during PE classes. Furthermore, after controlling for students’ autonomous motivation and perceived autonomy support from their teachers, students in the experimental group, compared to those in the control group, will spend higher percentages of time in MVPA during three lessons when the intervention is applied.

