#### Secondary outcomes

Secondary outcomes include students’ time spent in sedentary, light, moderate, and vigorous physical activity as measured by accelerometry, and defined using Evenson et al.’s [25] cut-points. Perception of autonomy support provided by their teachers during the last four PE lessons, and their motivation (autonomous and controlled) during the last four PE lessons were also measured as secondary outcomes. Psychological variables will be measured using self-reported questionnaires administered using pen and paper at the end of Lesson 4 (baseline) and Lesson 8 (post-test). Specifically, the 6-item version of the Learning Climate Questionnaire [28] will be used to measure students’ perceived autonomy support provided by their teachers. The original scale in English was translated into Chinese using a back-translation protocol. As the translated scale has not previously been used, factorial validity of responses will be examined before the main analyses are conducted. In terms of motivation orientations, the Chinese Perceived Locus of Causality Questionnaire (PLOCQ) [29] will be used to measure autonomous and controlled motivation. Evidence of validity and reliability of the scale scores has been shown by Lonsdale et al. [29]. As motivational factors are likely to differ across individuals, students’ motivation towards PE was considered as a variable at the individual level. In contrast, as perceived autonomy support is referenced to the same teacher, the mean scores within each cluster will be aggregated to form an indicator representing this construct at the cluster level.

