### Statistical methods

Multilevel modeling will be used to account for the effects of participant clustering. Specifically, a three-level (time within student within class) model will be examined. For our primary outcome of students’ percentage time spent in MVPA, the effects of group allocation and student gender on percentages of time spent in MVPA will be examined using a multilevel regression model. The group × gender interaction effect will also be examined to determine whether the effect of the intervention is homogeneous across genders. Further, we will also examine a model by adding perceived autonomy support, autonomous and controlled motivation as potential confounders of the outcome. Two-tailed tests with an alpha level of .05 will be used to determine the significance of all results. To examine whether the intervention would lead to changes in motivation variables and perceived autonomy support by teachers, these variables will be regressed on group, gender, and group × gender in an additional series of three-level regression analyses. Statistical analyses of the study will be conducted by a statistician blinded to the hypotheses of the study and to each class’ allocation to the experimental or control condition.

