Based on our knowledge, this is the first intervention designed specifically to increase students’ MVPA during PE lessons in space confined environments. Apart from MVPA, we proposed to simultaneously examine the effects of the intervention on students’ autonomous and controlled motivation towards PE, as specified by SDT [14]. Based on the theory, these outcomes have important ramifications to students’ future engagement in PA, and also their physical and psychological well- and ill-being. Accordingly, we hypothesize that the intervention would increase students’ MVPA during PE, and also support more adaptive forms of motivation. In this study we also proposed to measure the perceived autonomy support and control by PE teachers. Within SDT, these perceptions are important predictors of students’ motivation towards PE, and in turn the amount of MVPA they engage in class. Our study will provide preliminary evidence on the relation between perceived teacher behaviors and students’ objectively measured activity levels. Further, our results could inform future research directions in terms of methods to further improve PE intervention effectiveness. For instance, future work could investigate whether the intervention could also further enhance students’ autonomous motivation if teachers were given training to be more autonomy supportive [33]. In conclusion, the results from our study may advance both teaching practices and theory alike.

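### The MVPA hypothesis is stated after adjustment for motivation and autonomy support, while the main objective, effectiveness criterion, leading model and sample size use a contrast without them

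*Protocol article*

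**What the plan says.** All places are in the protocol article.

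- **Objectives of current study, opening:** "The main objective of the current trial is to examine whether the implementation of a 15-minute rope skipping activity at the start of PE lessons" raises the share of class time in MVPA. No adjustment is named.
- **Objectives of current study, last sentence:** the only hypothesis there that links group to MVPA is conditional. "after controlling for students’ autonomous motivation and perceived autonomy support from their teachers, students in the experimental group" are to exceed controls on MVPA over three intervention lessons.
- **Abstract, Methods/Design:** effectiveness is judged by "comparing changes in the proportion of lesson time spent in MVPA from baseline to follow-up across the experimental and control groups".
- **Statistical methods:** for the primary outcome, "the effects of group allocation and student gender on percentages of time spent in MVPA will be examined using a multilevel regression model", with a group by gender interaction. The text then says: "Further, we will also examine a model by adding perceived autonomy support, autonomous and controlled motivation as potential confounders of the outcome". A single two-tailed .05 level covers every result.
- **Sample size:** an independent-samples t-test at d = 1.0 gives 34 students. This is inflated for clustering to 163, hence 24 classes of 7.
- **Discussion:** "we hypothesize that the intervention would increase students’ MVPA during PE, and also support more adaptive forms of motivation", again without conditioning.
- **Secondary outcomes:** autonomous and controlled motivation and perceived autonomy support are themselves secondary outcomes. They are collected by questionnaire at the end of Lesson 4 (baseline) and of Lesson 8 (post-test).

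**The concern.** One primary outcome has two group coefficients attached to it. The sentence that reads as the trial's hypothesis points to the adjusted one, and nearly everything else points to the unadjusted one. The covariate sets do not match either: the hypothesis names two variables and the second model three.

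A report that follows the hypothesis literally and a report that follows the leading model could differ on whether the intervention worked, and the choice could be made after both p-values are known. The hypothesis as written is also not the contrast for which the trial was sized.

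The stakes are higher if the post-test questionnaire enters the model. The section on motivational determinants counts a rise in autonomous motivation as part of a successful intervention. Holding that variable fixed at its post-test value would remove from the group coefficient whatever part of the MVPA gain came with it.

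**Working it through.** **1. The places side by side**

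| Place | Contrast | Psychological covariates |
|---|---|---|
| Main objective | effect of the activity on MVPA | none |
| Hypothesis in Objectives | group difference, conditional | autonomous motivation, autonomy support |
| Abstract | group difference in change | none |
| Statistical methods, leading model | group, gender, interaction | none |
| Statistical methods, second model | same, plus covariates | autonomous and controlled motivation, autonomy support |
| Sample size | two-sample t-test | none |
| Discussion | effect on MVPA | none |

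**2. The plan's own figure.** Inputs from Sample size: d = 1.0, two-sided alpha .05, power .80, m = 7, ICC .63. By the noncentral t, 16 per arm gives power 0.781 and 17 per arm gives 0.807, so N = 34. The design effect is 1 + (7 − 1) × 0.63 = 4.78. Then 34 × 4.78 = 162.5, rounded up to 163, and 163/7 = 23.3, rounded up to 24 classes. The figure reproduces, and it belongs to the contrast without covariates.

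**3. Power of that contrast with 24 classes.** Effective size per arm is 84/4.78 = 17.6. With 22 df, power is 0.81.

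**4. What the adjusted coefficient estimates.** Write total effect = direct effect + (covariate slope × group shift in the covariate).

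- *Lesson 4 values only.* These are labelled baseline, and they precede the teacher workshop. The expected group shift is zero, so both models target the total effect.
- *Lesson 8 values.* These follow randomization, and the shift need not be zero. The adjusted coefficient is then the direct part only.

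The article does not say which values enter. The planned model has time within student, and the covariates are measured at both times, so the Lesson 8 reading is open.

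The article gives no slope or shift. Taking the share of the effect carried by the covariates as an assumption, with total d = 1.0 and the standard error unchanged:

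| Share carried | Power of adjusted contrast |
|---|---|
| 0% | 0.81 |
| 10% | 0.72 |
| 20% | 0.62 |
| 30% | 0.51 |
| 50% | 0.29 |

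**5. How often the two tests disagree** (one significant at .05, the other not).

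Set A: 10,000 simulated trials per row, 12 against 12 class means, class-mean variance 0.63 + 0.37/7 = 0.683, one class-level covariate, *total* effect 1.0.

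| Shift (SD) | Slope | Unadjusted only | Adjusted only | Disagree |
|---|---|---|---|---|
| 0 | 0 | 0.035 | 0.012 | 0.047 |
| 0 | 0.3 | 0.027 | 0.059 | 0.086 |
| 0.5 | 0.3 | 0.134 | 0.015 | 0.149 |
| 0.8 | 0.3 | 0.257 | 0.004 | 0.261 |

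Set B: 4,000 simulated trials per row, class means regressed on group alone and on group plus class-mean autonomous motivation and autonomy support, *direct* effect 1.0. Its slopes are not reported here, so it serves as a second range rather than a calculation to repeat.

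| Effect on motivation and autonomy support | Power unadjusted | Power adjusted | Disagree |
|---|---|---|---|
| none | 0.785 | 0.756 | 0.097 |
| 0.3 SD | 0.842 | 0.726 | 0.141 |
| 0.5 SD | 0.894 | 0.700 | 0.205 |

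Together the sets give about 5% to 10% disagreement with no shift, and about 14% to 21% with shifts of 0.3 to 0.5 SD. The no-shift rows also describe adjustment for Lesson 4 values only.

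**6. Error rate.** With no total effect and no shift, the chance that at least one of the two tests is significant is 0.043 + 0.009 + 0.008 = 6.0% at slope 0 in set A, rising to 7.6% at slope 0.5. Inflation from the choice is slight.

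**Limits.** Both sets work on class means and leave out gender, controlled motivation, baseline MVPA and the pair matching. The article treats motivation as an individual-level variable.

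**The case against.** The strongest reply is that the article already shows which contrast it means. Statistical methods attaches the primary outcome to the group-and-gender model and brings in the other as a further analysis. The main objective, abstract, sample size and Discussion agree. On this view one sentence is out of line, and an explicit label for the primary model may be left to a fuller analysis plan. Most of this stands. A reader might infer two equal candidates for the primary test, and the text does not support that. What remains is a stated contradiction rather than a missing detail: the hypothesis in the Objectives names a different contrast.

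A reader might also infer that the two models necessarily estimate different quantities. They do so only if post-randomization values enter. Describing the covariates as potential confounders is compatible with using Lesson 4 values.

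It is also fair that the article does not claim the intervention raises MVPA through motivation. The Discussion describes autonomy support predicting motivation and, in turn, MVPA, and leaves autonomy-support training to future work. The workshop teaches skipping skills and ways to keep students active. Any shift of 0.3 to 0.5 SD is therefore an assumption. Against that, Statistical methods plans to test whether the intervention changes these variables, so a shift cannot be excluded in advance.

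**Conclusion.** The contradiction is real and worth correcting. The hypothesis in the Objectives is conditional on autonomous motivation and autonomy support, five other places use a contrast without them, and the second model adds a third covariate. The article leans clearly to the unadjusted contrast.

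The consequence depends on timing. With Lesson 8 values, the adjusted test can miss an effect that the unadjusted test finds. With Lesson 4 values only, the difference is mainly precision. At d = 1.0 the tests disagree in about 5% to 10% of simulated trials with no effect on motivation, and in about 14% to 21% with assumed effects of 0.3 to 0.5 SD.

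A reader might infer that modest effects on motivation would split the verdicts in more than a quarter of trials. They do not: 26% needs a 0.8 SD shift, and 28% (power 79% against 51%) came from a run with d lowered to 0.8 and a stronger motivation path. Disagreement here means one p-value on each side of .05, not effects in opposite directions. The sample size needs no change on this point.

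**What to change.** 1. In Objectives of current study, remove the conditioning clause, so that the hypothesis is that the experimental group spends a higher percentage of lesson time in MVPA than the control group.
2. In Statistical methods, state that effectiveness is decided by the between-group difference in change in MVPA proportion, from the model without autonomous motivation, controlled motivation or perceived autonomy support.
3. Label the model with those variables as supportive or explanatory, with no bearing on the effectiveness verdict, and say whether Lesson 4 or Lesson 8 values enter it.

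The cost is about one sentence in each of the two sections. No data, analysis or sample size is added.

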## Methods/Design

### Trial design

A cluster randomized controlled trial will be conducted to evaluate the impact of the rope skipping intervention on MVPA in PE lessons. A flow diagram and timeline of the design protocol are shown in Figures 1 and 2, respectively. Randomization will be carried out at the class level. Allocation ratio of experimental and control groups will be set at 1:1. Each class will be defined as a separate cluster. All procedures of the study will be carried in compliance with the Helsinki Declaration. Ethic approval for the study protocol was obtained from the Joint Chinese University of Hong Kong-New Territories East Cluster Clinical Research Ethics Committee (Reference: CRE-2013.235).

